**b) Hypothesis**

Delivery by electroporation will improve the immunogenicity of ADVAX in healthy volunteers.

**c) Objectives**

***Primary:***

- To evaluate the safety of an intramuscular prime and boost injection of the ADVAX DNA-based HIV vaccine via TriGrid™ electroporation at all three dosing levels

***Secondary:***

- To evaluate the immunogenicity of an intramuscular prime and boost injection of the ADVAX DNA-based HIV vaccine via TriGrid™ electroporation compared to placebo or standard syringe injection at all three dosing levels
- To evaluate the immunogenicity of an intramuscular prime and boost injection of the ADVAX DNA-based HIV vaccine via TriGrid™ electroporation at three dosage levels at all three dosing levels

**d) Primary Endpoints**

**Safety and Tolerability**:

- Severe local reactogenicity events (pain, tenderness, erythema/skin discoloration, edema, damage [vesiculation/ulceration], induration, formation of a crust or scab.
- Severe systemic reactogenicity events (fever, chills, headache, nausea, vomiting, malaise, myalgia, arthralgia, rash).
- Severe other adverse events (including laboratory abnormalities).
- All Serious Adverse Events.
- Proportion of volunteers with mild and moderate local and systemic reactogenicity events.
- Electroporation Tolerability Assessment Questionnaire Responses (Appendix B)

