**APPENDIX C: ADVERSE EVENT SEVERITY ASSESSMENT TABLE**

| **PARAMETER** | **MILD** | **MODERATE** | | **SEVERE** | |
| --- | --- | --- | --- | --- | --- |
| **General Principle for Severity Assessment** | Mild discomfort. Minimal or no limitation of daily activity.  No need for medical intervention. | Moderate discomfort.  Some limitation of daily activities (e.g. able to work part-time)  May require minimal or no medical intervention | | Severe discomfort. Marked limitation of daily activities (e.g. unable to work). Requires medical intervention. | |
| **LOCAL REACTOGENICITY:** | | |  | |  |
| **Pain and tenderness** | Minimal discomfort associated with minimal or no limitation of use of arm | Moderate discomfort with some limitation of use of arm causing some interference with daily activities. May require single dose of analgesic or NSAID. | | Severe discomfort with significant limitation of use of arm causing marked limitation of daily activities (e.g. unable to work). Requires medical intervention (e.g. repeated doses of analgesic or NSAID). | |
| **Erythema (redness) or skin discoloration** | Light red blush up to 25% of the circumference of the upper arm | Marked redness involving up to 50% of the circumference of the arm | | Brick red involving >50% of the circumference of the upper arm | |
| **Edema (swelling)** | Light edema involving up to 25% of the circumference of the upper arm | Marked edema involving up to 50% of the circumference of the arm | | Significant edema >50% of the circumference of the upper arm | |
| **Induration** | Hardening under the skin <1.5 cm in diameter | Hardening under the skin 1.5-3.0 cm in diameter | | Hardening under the skin >3.0 cm in diameter | |
| **Skin damage (vesicle, ulcer)** | Vesicles or superficial disruption of epithelium < 1 cm | Vesicles or superficial disruption of epithelium 1-2 cm | | Full thickness disruption of the epithelium (ulceration) > 2 cm | |
| **Formation of crust, scab or scar** | Crust, scab or scar = 2cm | Crust, scab or scar 2­4cm | | Crust, scab or scar > 4cm | |

| **SYSTEMIC REACTOGENICITY** | |  |  |
| --- | --- | --- | --- |

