| **Headache** | Minimal headache causing no interference with daily activities | Moderate headache causing some interference with daily activities. May require single dose of analgesic or NSAID. | Significant headache causing marked limitation of daily activities (e.g. unable to work). Requires medical intervention (e.g. repeated doses of analgesic or NSAID). |
| **Rigor (chills)** | Minimal discomfort causing no interference with daily activities | Moderate discomfort causing some interference with daily activities | Significant discomfort causing limitation with daily activities (e.g. unable to work). |
| **Malaise (generalized feeling of discomfort)** | Minimal discomfort causing no interference with daily activities | Moderate discomfort causing some interference with daily activities | Significant discomfort causing limitation with daily activities (e.g. unable to work). |
| **Fatigue (tiredness)** | Minimal discomfort causing no interference with daily activities | Moderate discomfort causing some interference with daily activities | Significant discomfort causing limitation with daily activities (e.g. unable to work). |
| **Myalgia (other than vaccination site)** | Minimal muscle pain causing no interference with daily activities | Moderate muscle pain causing some interference with daily activities. May require single dose of analgesic or NSAID. | Significant muscle pain causing marked limitation of daily activities (e.g. unable to work). Requires medical intervention (e.g. repeated doses of analgesic or NSAID). |
| **Arthralgia** | Minimal joint pain causing no interference with daily activities | Moderate joint pain causing some interference with daily activities. May require single dose of analgesic or NSAID. | Significant joint pain causing marked limitation of daily activities (e.g. unable to work). Requires medical intervention (e.g. repeated doses of analgesic or NSAID). |
| **Fever** | 37.7–38.6°C (99.8– 101.5°F) | 38.7–39.3°C (101.6– 102.7°F) | >39.4°C (>102.8°F) |
| **Nausea** | Minimal nausea causing no interference with daily activities | Moderate nausea causing some interference with daily activities.. | Significant nausea causing marked limitation of daily activities (e.g. unable to work). |

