| **Vomiting** | Minimal nausea causing no interference with daily activities | Moderate nausea causing some interference with daily activities. | Significant nausea causing marked limitation of daily activities (e.g. unable to work). Requires medical intervention |
| --- | --- | --- | --- |
| **Pruritus** | Localized itching at vaccination site | Itching at the injected arm (beyond vaccination site) | Generalized itching |
| **Rash** | Localized maculopapular (non­urticarial) rash at the vaccination site area causing no interference with daily activities | Diffuse maculopapular (non-urticarial) rash at the injected arm (beyond vaccination site) causing some limitation of daily activities | Systemic maculopapular (non­urticarial) rash causing marked limitation of daily activities. Requires medical intervention |
| **Allergic reaction** | Localized urticaria at vaccination site causing no interference with daily activities | Diffuse urticaria at the injected arm (beyond vaccination site) and causing some limitation of daily activities | Systemic urticaria or angioedema causing marked limitation of daily activities. Requires medical intervention |
| **HEMATOLOGY** |  |  |  |
| Hemoglobin | 10.0 g/dL – 11.0 g/dL OR  any decrease = 2.5 g/dL | 9.0 g/dL – 9.9 g/dL OR  any decrease = 3.5 g/dL | = or <8.9 g/dL  OR  any decrease = 4.5 g/dL |
| WBC—Elevated WBC—Decreased | 13,000–14,999/mm3 | 15,000–19,999/mm3 | = or >20,000/mm3 |
| 2000–2499/mm3 | 1500–1999/mm3 | = or <1499/mm3 |
| Absolute Neutrophil Count | 1000–1300/mm3 | 750–999/mm3 | = or <749/mm3 |
| Absolute Lymphocyte Count | 600–649/mm3 | 500–599/mm3 | = or <499/mm3 |
| Absolute CD4 Count (HIV Negative) | 300–400/mm3 | 200–299/mm3 | = or <199/mm3 |
| Platelets—Decreased Platelets—Elevated | 100,000–124,999/mm3 | 50,000–99,999/mm3 | = or <49,999/mm3 |
| NA | 550,000–600,000/mm3 | > 600,000/mm3 |
| **CHEMISTRY** |  |  |  |
| BILIRUBIN (total) | 1.0–1.5 x ULN | >1.5–2.5 x ULN | >2.5 x ULN |
| CREATININE | 1.1–1.3 x ULN | >1.3–1.8 x ULN | >1.8 x ULN |
| AST (SGOT) | 1.51–3.0 x ULN | >3.0–6.0 x ULN | >6.0 x ULN |
| ALT (SGPT) | 1.51–3.0 x ULN | >3.0–6.0 x ULN | >6.0 x ULN |
|  |  |  |  |

| **URINALYSIS** | | |  | |  |
| --- | --- | --- | --- | --- | --- |
| PROTEINURIA | 1+ (30 mg/dL) | 2–3+ (100-500mg/dL) | | 4+ (> 500mg/dL) | |
| Random urine 24-hour urine | 200 mg–500 mg loss/day | > 500 mg–1.0 g loss/day | | > 1.0g loss/day | |

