**APPENDIX D: Volunteer Diary Card**

**Volunteer Diary Card**

**Protocol DHO-0614-0707**

Volunteer ID Number

Date and time of injection

Date of Next Visit:

Name of Study Contact:

24 HOUR EMERGENCY telephone number to report any unusual or severe symptoms that occur before the next visit:

** Please bring this card to your next clinic visit.

If you experience any symptoms following this vaccination that persist beyond day 3 (72 hours) please indicate the severity for each one noted in the column under the day you noticed the symptom. Unless an item says MEASURE, please rate severity as “-“for none, “+” for mild, “++” for moderate, or “+++” for severe.

| **Code** | **Meaning** |
| --- | --- |
| - | Symptom not present |
| + | Mild: Transient or mild discomfort, no limitation in normal daily activity |
| ++ | Moderate: Some limitation in normal daily activity |
| +++ | Severe: Unable to perform normal daily activity |

| **Possible Symptoms** | **Date** | **Date** | **Date** | **Date** | **Date** | **Date** | **Date** |
| --- | --- | --- | --- | --- | --- | --- | --- |
| Local Symptoms  Pain (pain without area being touched) at injection site |  |  |  |  |  |  |  |
| Tenderness (pain when area being touched) at injection site |  |  |  |  |  |  |  |
| Redness (erythema) at injection site  MEASURE | mm | mm | mm | mm | mm | mm | mm |
| Skin damage (vesicles, ulcers) at injection site  MEASURE | mm | mm | mm | mm | mm | mm | mm |
| Hardness or thickening (induration) at injection site MEASURE | mm | mm | mm | mm | mm | mm | mm |
| Swelling (edema) at injection site |  |  |  |  |  |  |  |
| Formation of crust, scab or scar MEASURE | mm | mm | mm | mm | mm | mm | mm |
| Systemic Symptoms  Headache |  |  |  |  |  |  |  |
| Chills |  |  |  |  |  |  |  |
| Nausea |  |  |  |  |  |  |  |
| Vomiting |  |  |  |  |  |  |  |
| Temperature MEASURE  Measure before midnight of the date stated | °F | °F | °F | °F | °F | °F | °F |
| Feeling of general discomfort, uneasiness, a general sick feeling (malaise) |  |  |  |  |  |  |  |
| Muscle aches (myalgia) |  |  |  |  |  |  |  |
| Aching joints (arthralgia) |  |  |  |  |  |  |  |

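### Systemic reactogenicity has three different term lists (nine in the primary endpoint, twelve in Appendix C, eight on the diary card), and the primary mild/moderate proportion does not say which applies

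*Protocol*

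**What the plan says.** Section d) Primary Endpoints of the Protocol defines the severe systemic component by a bracketed list with no wording to mark it as examples: "Severe systemic reactogenicity events (fever, chills, headache, nausea, vomiting, malaise, myalgia, arthralgia, rash". A later bullet makes a second component primary, "Proportion of volunteers with mild and moderate local and systemic reactogenicity events", and gives no terms for it. The only catch-all bullet is limited to severe events: "Severe other adverse events (including laboratory abnormalities".

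Appendix C, which the adverse event section names as the table for assessing severity, has a block headed "SYSTEMIC REACTOGENICITY". It contains every endpoint term and three more: "Fatigue (tiredness", in a row separate from malaise; pruritus, whose mild grade is "Localized itching at vaccination site"; and allergic reaction, whose mild grade is "Localized urticaria at vaccination site causing no interference with daily activities".

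The Volunteer Diary Card has its own list of systemic symptoms. It has no row for fatigue, itching, urticaria or rash. Its malaise item reads "Feeling of general discomfort, uneasiness, a general sick feeling (malaise" and does not mention tiredness.

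The local lists differ by one word: the endpoint has crust or scab, while Appendix C and the diary add scar.

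**The concern.** The proportion with mild or moderate reactogenicity is a primary endpoint, so its numerator should be fixed by the protocol. The document offers three candidate lists and no rule for choosing among them. The choice matters for volunteers whose only systemic symptom is mild or moderate and is one of the three added terms. They count if the Appendix C heading defines systemic reactogenicity. They fall outside every primary component if the endpoint list does, because the catch-all bullet covers only severe events.

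Collection is also affected. Rash is a primary endpoint term under either list, yet the diary does not prompt for it. If the three extra terms are meant to count, they have no diary prompt either. An analysis plan can choose a list later, but it cannot recover daily entries that were never requested.

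**Working it through.** **Step 1. Count and compare the lists.**

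| Term | Primary endpoint | Appendix C systemic block | Diary card |
|---|---|---|---|
| Fever (temperature on diary) | yes | yes | yes |
| Chills | yes | yes | yes |
| Headache | yes | yes | yes |
| Nausea | yes | yes | yes |
| Vomiting | yes | yes | yes |
| Malaise | yes | yes | yes |
| Myalgia | yes | yes | yes |
| Arthralgia | yes | yes | yes |
| Rash | yes | yes | no |
| Fatigue | no | yes | no |
| Pruritus | no | yes | no |
| Allergic reaction | no | yes | no |
| **Total** | **9** | **12** | **8** |

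- In Appendix C but not the endpoint: fatigue, pruritus, allergic reaction.
- In the endpoint but not Appendix C: none.
- In the endpoint but not the diary: rash.

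**Step 2. Follow an event in one of the three extra terms through the primary endpoint.**

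- Severe: severe systemic reactogenicity under Appendix C, other severe adverse event under the endpoint list. It is primary either way and only changes category.
- Mild or moderate: in the primary proportion under Appendix C, in no primary component under the endpoint list.

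**Step 3. Check the interval method against the protocol's own figures.** The sample size section gives 95% upper bounds for zero related serious adverse events of 0.37, 0.21 and 0.14 at n = 8, 16 and 24. The two-sided Clopper-Pearson bound is 1 − 0.025^(1/n), which gives 0.369, 0.206 and 0.142. The figures agree. They concern a different endpoint, and nothing here depends on them.

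**Step 4. Effect of one volunteer.** Each electroporation dose group has 8 vaccine recipients (section f, Study Design), so one volunteer is 1/8 = 12.5 percentage points. For example, with 95% Clopper-Pearson intervals:

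- 1/8 = 12.5% (0.3% to 52.7%)
- 2/8 = 25.0% (3.2% to 65.1%)

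**Step 5. How often this might happen.** The documents give no rate. As an assumption, let q be the share of volunteers whose only systemic symptom is mild or moderate and is one of the three extra terms. The chance that at least one of 8 changes status is 1 − (1 − q)^8, and the expected number among the 24 ADVAX/EP volunteers is 24q:

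- q = 0.05: 34%; 1.2 volunteers
- q = 0.10: 57%; 2.4 volunteers
- q = 0.20: 83%; 4.8 volunteers

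These results apply to a systemic-only proportion. If local and systemic events are combined, any volunteer with injection-site pain or tenderness already counts. The risk section expects pain and soreness and says electroporation may increase such reactions, so few volunteers would change status.

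**The case against.** The strongest reply is that the two main lists do different jobs. The endpoint section defines endpoints, while Appendix C grades severity for all adverse events, including laboratory and organ-system events. All nine endpoint terms can be graded there, and a grading table wider than the endpoint list need not contradict it. On the ordinary reading, the mild/moderate bullet refers back to the nine terms. This has force, and it may be what the authors intended. But no text says so, and the Appendix C heading does class the three extra terms as systemic reactogenicity. It also does not explain why rash is missing from the diary.

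A second reply is that an agreed data analysis plan is foreseen and could settle which terms are tabulated. That is fair for the tabulation, but not for what the diary asks.

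Three stronger readings are tempting, and the documents do not support them:

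- **That events are lost from the safety record.** The analysis section reports all adverse events by severity and relationship and plans rates for both solicited and unsolicited events. Only a mild or moderate event's place in the primary proportion is in doubt.
- **That the three extra terms can surface only by spontaneous report.** Staff record reactogenicity and any other event 30 to 45 minutes after vaccination and assess it again at post-vaccination visits. Appendix A schedules the assessment at the telephone contacts too, and subjects are questioned or examined about adverse events at each outpatient visit. What remains is that terms without a daily prompt may be captured less completely; by how much is unknown.
- **That 34% to 83% is the chance that the primary result changes.** Those figures follow from an assumed rate and hold only for a systemic-only proportion.

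**Conclusion.** The inconsistency is real and can be checked on the page: nine, twelve and eight terms, with no statement of which list defines a systemic reactogenicity event in the primary mild/moderate proportion. Its consequence is confined to volunteers whose only systemic symptom is mild or moderate fatigue, itching or urticaria. Each one shifts a dose group's systemic-only proportion by 12.5 points, and a combined proportion would rarely move. How many volunteers are affected cannot be derived from the documents; the 5% to 20% range is an assumption. The diary's omission of rash is a separate, firmer point, because it does not depend on which of the other two lists governs.

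The impact is modest. The trial is descriptive and hypothesis-generating. No sample size figure depends on this, and neither do the dose-escalation reviews nor the suspension rule, which work from adverse event severity, relatedness and serious adverse events. The correction is still worth making: it concerns a primary endpoint and its collection form, and it is cheap.

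**What to change.** Use one list in section d), Appendix C and the diary card:

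1. Add a rash row to the diary in any case.
2. Choose one of two routes for fatigue, pruritus and allergic reaction. Either add them to the section d) list and to the diary, or move their rows out of the systemic reactogenicity block of Appendix C and report them as unsolicited adverse events.
3. State that the mild/moderate bullet uses this same list, and whether the proportion is reported for local and systemic events separately, combined, or both.
4. Align the local wording on crust, scab and scar across the three places.

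The cost is protocol wording and between one and four extra diary rows, with no new visits. If the three terms are added, the reported mild/moderate rate may be slightly higher.

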**e) Secondary Endpoints**

**Immunogenicity:**

Immunogenicity analyses will include:

- HIV-1 specific T-cell responses as quantified by IFN-ELISpot

- HIV-1 specific T-cell responses as quantified by multiparametric cytokine flow cytometry (CFC)
- Binding and neutralizing HIV antibody responses in blood and mucous secretions
- Additional studies as warranted at the discretion of the investigators.
- All immune responses will be evaluated for proportion of responders and the mean responses will be compared.

**f) Study Design**: The study is a Phase I pilot study that involves the administration of two injections of ADVAX vaccine or placebo, (with an optional third vaccination of ADVAX or placebo to the high dose EP cohort) that will be administered intramuscularly with or without electroporation to a total of forty healthy volunteers. The ADVAX vaccine with electroporation will be administered at three different dose groups, to eight individuals per dose group. ADVAX IM without electroporation will be administered at the highest dose (4mg) to volunteers. Eight volunteers will receive placebo. *An over-enrollment of 10% will be permitted.

| **Group** | **Dose** | **Material/Route** | **Subjects*** |
| --- | --- | --- | --- |
| **Group 1** | **0.2 mg** | **DNA /EP** | **8** |
| **Group 2** | **1 mg** | **DNA/EP** | **8** |
| **Group 3** | **4 mg** | **DNA/EP** | **8** |
| **Group 4** | **Saline** | **Saline/EP** | **8** |
| **Group 5** | **4 mg** | **IM** | **8** |

Safety and tolerability of the ADVAX vaccine will be evaluated after the two vaccinations given at Day 0 and Week 8 and at follow-up visits at 1, 2 ,4 weeks post the first vaccination and at weeks 9, 10 and 12 post second vaccination then at weeks 16, 24, 36, 48 and 56 post vaccinations. The eleven volunteers in the high dose EP cohort will be offered an optional third vaccination at week 36, with additional follow up visits at weeks 37, 38, 40, and 44.

Volunteers will be screened up to 42 days prior to enrollment and first vaccination and will be followed for 12 months after the second vaccination.

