**g) Statistical Model**

Randomization: will take place as indicated in the following table

| **Group** | | |  |
| --- | --- | --- | --- |
| **Placebo**  **(Saline/EP)** | **ADVAX IM** | **ADVAX/EP** | **DSMB evaluation prior to advancement** |
| **2** | **2 High Dose** | **8 Low Dose** | **12/12 subjects have received 1 vaccination**  **8/12 have received 2 vaccinations** |
| **3** | **3 High Dose** | **8 Mid Dose** | **14/14 subjects have received 1 vaccination**  **8/14 have received 2 vaccinations** |
| **3** | **3 High Dose** | **8 High Dose** |  |
| **8** | **8** | **24** | **Total Subjects** |

The randomization process will be performed by the Research Pharmacist at the Rockefeller University utilizing http://www.randomization.com.

The statistician at the Data Coordinating Center (EMMES Corporation), in collaboration with the principal investigators (or designees), will create tables according to a data analysis plan that has been reviewed and agreed to by the principal investigators (or designees). The EMMES Corporation will conduct the data analysis and will provide interim and final study reports for the principal investigators (or designees) and the regulatory authorities as appropriate. Prior to an analysis, additional monitoring visits will take place if necessary to validate the data held on the database, as well as all consent forms and dispensing records. Data files will be prepared by EMMES from a ‘frozen’ dataset for that particular analysis.

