## Sample Size and Power Calculations

A minimum of 40 volunteers will be enrolled in the study; 32 volunteers will be given active vaccines (24 EP and 8 IM) and 8 volunteers will be given placebo via EP route. An over-enrolment of about 10% (4 volunteers) will be permitted. This small sample size is appropriate for an exploratory dose-escalation study of a novel product while safety and immunogenicity of the vaccine are investigated.

The rate of Serious Adverse Events related to vaccine will be used as one measure of the safety of the candidate vaccine. Adverse Events that may be temporarily incapacitating (for example, loss or cancellation of work or social activities), which could make a vaccine impractical for large scale use if they occur in more than a small proportion of cases, will also be assessed.

One method of assessing the sample size is to consider the precision for estimation of incidence of serious adverse events.

*Prior to the enrollment of the medium dose level group:*

If none of the volunteers receiving the vaccine experiences an SAE related to vaccine (n=8), the 95% upper confidence bound for the rate of these adverse events in the population is 0.37 by Clopper Pearson method.

*Prior to the enrollment of the highest dose level group:*

If none of the volunteers receiving the vaccine experiences an SAE related to vaccine (n=16), the 95% upper confidence bound for the rate of these adverse events in the population is 0.21.

*After all volunteers have received the initial dose:*

If none of the volunteers receiving the vaccine experiences an SAE related to vaccine (n=24), the 95% upper confidence bound for the rate of these adverse events in the population is 0.14.

There is very limited power for comparison of event rates between treatment arms.

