**A Data and Safety Monitoring Board has been composed to oversee data and safety for the Rockefeller/ADARC site.**

## Standard Operating Procedures (SOPs) for the Data and Safety Monitoring Board (DSMB):

- The charter of the DSMB is to provide an ongoing assessment of volunteer safety during the ADVAX + EP Clinical Trial. The DSMB will consist of independent individuals who have no relationship to the Principal Investigator and Co-Investigators involved in the trial. No member of the DSMB will have any direct responsibility for the clinical care of trial volunteers. No representative of IAVI, Ichor or ADARC or their designees may be a member of the DSMB. However, the DSMB may invite the principal investigator (PI) or designee and an IAVI and/or ADARC representative to an open session of a DSMB meeting to provide information on study conduct, present data, or to respond to the members’ questions.
- The names, university affiliation and title, area of expertise, and contact information of each of the DSMB members are provided to the IRB (as listed above).
- All updated versions of the protocol and Investigator Brochure (I.B.) will be provided to the DSMB members.
- The DSMB will teleconference to review the trial data at least 14 days after both of the following criteria have occurred in the first group: after 12 volunteers in the first group have received their first vaccination *and* at least 8 volunteers in the same group have received both vaccinations. Similarly for group two, the DSMB will teleconference after 14 volunteers in the second group have received their first vaccination *and* at least 8 volunteers in the same group have received both vaccinations before proceeding to the next dose group. The DSMB must approve escalation to the next dose. At least two members are required to review the data before approval. Additional meetings will take place if there are indications for an interim review, which may be unblinded at the discretion of the DSMB.
- The study team will provide the DSMB with updated records of all adverse events (AEs) of a grade 2 or higher prior to each teleconference. The DSMB will be asked to review all severe clinical adverse/reactogenicity events judged by the Principal Investigator or designee to be possibly, probably or definitely related to vaccine.

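### The optional third 4 mg electroporation dose at Week 36 has no scheduled DSMB review of two-dose 4 mg electroporation data before it

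*Protocol*

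**What the plan says.** *The third dose.* Protocol, f) Study Design: "The eleven volunteers in the high dose EP cohort will be offered an optional third vaccination at week 36". The rationale section explains why. Mouse data favoured three EP vaccinations over two, and two vaccinations had so far been safe and tolerable in people at every dose level. No board review is cited for that statement.

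*The scheduled reviews.* The DSMB standard operating procedures set two teleconferences. The first follows the low dose group, once all 12 volunteers have had dose 1 and at least 8 have had both doses, with a lag of at least 14 days. The second follows the mid dose group on the same pattern with 14 volunteers, before the next dose group starts. The table in g) Statistical Model agrees; its mid dose row includes "8/14 have received 2 vaccinations". That column concerns advancement and has no entry in the high dose row.

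*What approval covers.* "The DSMB must approve escalation to the next dose", and "At least two members are required to review the data before approval".

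*What reaches the board.* Before a call the board receives "updated records of all adverse events (AEs) of a grade 2 or higher prior to each teleconference". Separately, "The DSMB will be asked to review all severe clinical adverse/reactogenicity events judged by the Principal Investigator or designee"; this applies where that judgement is of at least a possible link with the vaccine. Severe laboratory events go to it on an interim basis if confirmed on retest and judged related. Additional meetings are possible when indicated.

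**The concern.** If only two doses were given, nothing would follow the high dose stage, and a schedule ending with the approval to start it would be reasonable. The optional Week 36 dose adds a step. It produces the highest cumulative EP exposure in the trial, in healthy volunteers, with a device that the Data and Safety Monitoring Plan describes as not previously used in healthy people. The two earlier steps up in EP dose each needed board approval on data that included volunteers with both vaccinations. This step needs none.

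The events affected are grade 2 events and severe events judged unrelated. Grade 2 events matter here: the proportion of volunteers with moderate reactogenicity is among the primary endpoints, and Appendix C defines moderate as involving some limitation of daily activities. A pattern of such events after two 4 mg EP doses would be relevant to whether a third should be offered. The board may also unblind, so it is well placed to compare ADVAX by EP with saline by EP.

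**Working it through.** **1. The plan's figure of eleven.** The high dose stage allocates 3 saline EP, 3 ADVAX IM and 8 ADVAX EP (g) Statistical Model). Those randomized to EP number 3 + 8 = 11, which reproduces the stated figure; 8 of the 11 receive ADVAX. Permitted over-enrolment could change these counts slightly.

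**2. What the two scheduled reviews can contain.** All IM injections are 4 mg at every stage.

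| Cumulative ADVAX volunteers | Review 1 (after low dose stage) | Review 2 (after mid dose stage) | Planned total |
|---|---|---|---|
| EP at 0.2 or 1 mg | 8 | 8 + 8 = 16 | 16 |
| IM at 4 mg | 2 | 2 + 3 = 5 | 8 |
| EP at 4 mg | 0 | 0 | 8 |

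Review 2 must precede the high dose stage, so the zero in the last row follows from the schedule.

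**3. Exposure added.** Two doses: 2 × 4 = 8 mg. Three doses: 3 × 4 = 12 mg. Increase: 4/8 = 50%.

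**4. Routes to the board once 4 mg EP dosing has begun.**

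| Event in the 4 mg EP group | Route before Week 36 |
|---|---|
| Severe clinical, judged related | Event-driven DSMB review |
| Severe laboratory, confirmed and judged related | Interim DSMB review |
| Related SAE or severe AE, clinically significant, in 3 or more trial volunteers | Suspension and DSMB review |
| Severe, judged unrelated | None scheduled; ad hoc meeting only |
| Grade 2 | None scheduled; ad hoc meeting only |

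**5. Is there time for a review?** Doses 2 and 3 are (36 − 8) × 7 = 196 days apart. (One sentence under Post-Vaccination Visits puts the third dose at Week 38; Week 36 is used here, as elsewhere in the protocol.)

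Let g be the days between the first and last high-dose EP volunteers' Day 0, and t the days needed for the call and written report. The protocol gives neither. The first Week 36 visit falls on day 252 and the last second dose on day g + 56. With the 14-day lag:

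- On nominal dates: g ≤ 252 − 56 − 14 − t = 182 − t.
- With the Appendix A windows read as plus or minus (7 days at Week 36, 4 at Week 8) and taken unfavourably: g ≤ 245 − 60 − 14 − t = 171 − t.

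Assuming t is 7 to 14 days, the limits are 175 and 168 days on nominal dates, and 164 and 157 days with the windows. Complete two-dose data could be reviewed in time if the group enrols within about 157 to 175 days.

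**The case against.** The strongest reply is that the third dose repeats a dose already given twice, is voluntary, comes 196 days after dose 2, and was proposed with reference to human experience. The rationale's statement about all dose groups suggests that two-dose 4 mg EP data were already in hand. The board also learns of the plan: "All updated versions of the protocol and Investigator Brochure (I.B.) will be provided to the DSMB members". Other safeguards exist:

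- The first four EP volunteers in each dose group are staggered.
- Volunteers with injection reactions of Grade 3 or higher are removed.
- Site staff check each volunteer before each vaccination, and the clinical team discusses abnormal laboratory results weekly.
- The IRB receives SAEs and unexpected events within two working days.
- The safety analysis text mentions Safety Review Board review of relationship to vaccine for all adverse events.

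Most of this stands, and it keeps the priority low. It does not close the gap. Receiving a protocol version is not a data review. The rationale does not say that the board looked at the data behind its statement. The Safety Review Board sentence gives no timing and does not define that board.

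A reader might infer more than the text supports:

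- *That the board cannot see 4 mg EP data before Week 36.* It can, through event-driven review or an additional meeting, and grade 2 records would accompany any such call.
- *That the protocol breaks its own rule.* The approval requirement concerns escalation, and dose 3 is not an escalation in dose level.
- *That the blank high dose cell is an error.* It sits under a heading about advancement, and no stage follows.
- *That the sample-size line beginning "After all volunteers have received the initial dose" is a planned safety look lacking a board review, or that its confidence bounds measure this gap.* It illustrates precision for vaccine-related SAEs. The gap concerns moderate events and unrelated severe ones, and the protocol itself warns that EP may make local reactions more frequent or more severe, so a zero-event bound does not suit moderate local events.
- *That animal safety support is missing.* The rabbit study gave three 4 mg EP doses.

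**Conclusion.** The point holds as a limited gap in the monitoring schedule. Neither of the two scheduled teleconferences can include any of the 8 volunteers on ADVAX 4 mg EP, and no approval is tied to the Week 36 dose. Eleven volunteers would be offered it without a scheduled board look at grade 2 events, or severe events judged unrelated, after two 4 mg EP doses.

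The schedule fact is certain from the text. The practical consequence is less so: it depends on whether such events occur and whether anyone calls an extra meeting. Whether complete two-dose data would be ready in time rests on unstated accrual and the assumed 7 to 14 day turnaround. Low-priority point to consider.

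**What to change.** Add one teleconference to the DSMB operating procedures, and a matching new entry to the table in g) Statistical Model, covering the available two-dose 4 mg EP safety data: adverse events of grade 2 or higher and laboratory results. Keep the present terms, at least 14 days after the second vaccinations and at least two members reviewing. Require DSMB approval before the first Week 36 vaccination. If accrual means that complete two-dose data are not available by then, the board reviews what is available.

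The cost is one call of an existing board and two text changes, with no added visit, sample or volunteer. The downside is a possible short wait for the first optional dose, which could use part of the 7-day Week 36 window.
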